### Ethics approval

Institutional review board approval of the study protocol was obtained by the Medical Ethics Committee of the University Medical Center Groningen, Groningen, the Netherlands (2018.687). The study is designed and performed in accordance with the International Conference of Harmonization Good Clinical Practice Guidelines and with the principles of the Declaration of Helsinki.

### Study organization and study status

An advisory board including healthcare professionals from primary and secondary care will be consulted for advice on the design and conduct of the study. A central study team from the University Medical Center Groningen coordinates the study, with support from a regional team for local logistical issues. An independent and qualified data monitor will verify the participants’ rights, well-being, and safety, as well as the quality of the data.

The study started in November 2019. A total study time of one year for the home-based screening and elaborate screening was foreseen, but due to the COVID-19 pandemic, the study was temporarily halted and therefore delayed. Data collection is ongoing at the moment.

## Discussion

The present study will evaluate the participation rate, yield and cost-effectiveness of home-based screening for albuminuria in the general population. The importance of screening for albuminuria has been emphasized in recent years, as elevated albuminuria has increasingly been recognized as an early marker for both progression of CKD and generalized vascular endothelial damage. This holds, however, for patients with known type 2 diabetes or hypertension. Currently, only low-quality evidence is available on the benefits and harms of population screening for albuminuria in asymptomatic individuals. The THOMAS study is designed to address this knowledge gap prospectively.

In this screening study’s design, several choices were made that merit discussion. Regarding the study region, the region of Breda was chosen because the characteristics of its population closely resemble those of the average Dutch population concerning sex, age, and socioeconomic status distribution [16]. Its settings also reflect most Dutch towns, with an urban center harboring around 200.000 inhabitants and rural surroundings. Moreover, this region has not yet been subjected to large-scale screening efforts in the past.

Regarding the age thresholds of the study population, limiting screening for albuminuria to those aged ≥50 years has been suggested to be the most cost-effective considering the age-dependent prevalence of CKD [13,14]. As advancing age might reduce the chance that the benefits of screening will exceed its harms, most of the Dutch population screening programs use the age of 75 years as upper age limit, for instance for colorectal as well as for breast cancer screening [27,28]. In the present study, a slightly wider age range of 45–80 years was chosen to investigate the most cost effective and cost-effective age range.

It was decided to invite the total general population for the screening. It could be considered to screen only subjects not known yet with CKD and CVD risk factors. Indeed, in such patients, the benefits of screening may be most optimal. However, logistically it is difficult to delineate which subjects should be invited in this scenario. In the Netherlands, as in most countries, information on CKD and CVD risk profile is not readily available in a central database because of privacy considerations. Additionally subjects with known, but poorly controlled risk factors will be found that will benefit from optimizing treatment, by inviting the general population. Furthermore, by inviting the general population, the study will provide up-to-date information concerning albuminuria and CKD prevalence in the Netherlands.

As discussed earlier, the cost-effectiveness of albuminuria screening performed by GPs has been questioned [12–14]. Therefore, we designed a home-based albuminuria screening strategy with subsequent screening by GPs of only those with proven elevated albuminuria. With such a strategy, the burden on primary care will be reduced. Moreover, the costs will be lower, likely resulting in a cost-effective scenario [15].

In the present study, two home-based methods to assess albuminuria will be investigated. The UCD-method has the advantage of accurate measurement of albuminuria with immuno-turbidimetry, whereas the App-based dipstick method has the advantage of being able to communicate directly with participants on the results and consequences of these results, which may optimize participation. Both methods are easily accessible strategies for investigating albuminuria in the home situation.

It was decided to use an EMV sample and not 24-hour urine collections for the measurement of albuminuria. Although assessment of 24hr urinary albumin excretion is considered the gold standard for detecting albuminuria, collecting a 24-hour urine sample is not feasible for large scale population screening because it is time-consuming and inconvenient for participants. Instead, an EMV sample was chosen to measure the ACR, as this is more acceptable and shown to be better correlated with 24hr UAE than ACR in a random spot urine sample [29].

The ACR cut-off to indicate elevated albuminuria was set at 30 mg/g and 3 mg/mmol, in accordance with the prevailing KDIGO guideline [23]. The present study will, however, also investigate in a sensitivity analysis the effect of lowering the cut-off value for the first ACR test on the yield of the home-based screening. Such a strategy may lower the number of false negatives but on the other hand, increase the false positivity rate.

For the determination of the sample size, an overall participation rate of 50% is assumed. This is based on the experience from the PREVEND study. This observational, epidemiological study started in 1997 and aimed to study the natural course and consequences of elevated albuminuria in the general population. In total, 48% of the invited population participated and sent a test tube containing some urine collected at home to a central laboratory [7].

There are other important considerations that merit attention. First, this screening study is primarily focused on early identification of subjects with CKD. Therefore, not all subjects with CVD risk factors will be identified. Previous epidemiological analyses showed that people with newly discovered CVD risk factors, but no elevated albuminuria, on average have an absolute risk for CVD that does not merit start of cardioprotective treatment [11]. In contrast, subjects with newly discovered CVD risk factors and elevated albuminuria in general have such a high CVD risk that start of preventive treatment is indicated [11]. These data suggest that a screening primarily directed at discovering subjects with elevated albuminuria may be effective in discerning high-risk subjects for whom screening will have therapeutic consequences. Future studies could further investigate this. Second, the present study investigates the effectiveness of a single screening. Therefore, this study cannot directly demonstrate potential benefits regarding renal and CV event outcomes for repeated screening. However, the effectiveness of a repeat screening strategy can be modeled in the cost-effectiveness analyses. Third, it is assumed that the potential harms of the study are limited, because our screening strategy does not include invasive procedures. In addition, the psychological burden should be limited, because the diagnosis of CKD is based on an initial positive test that has to be confirmed, which by definition implies CKD. To further reduce potential psychological distress induced by the screening, all subjects will receive a brochure with detailed information including potential benefits and harms of participation. More information can be found on a dedicated internet site (www.niercheck.nl). Lastly, the UCD screening method uses the ACR cut-off of 3 mg/mmol for elevated albuminuria, whereas the App uses an ACR cut-off of 30 mg/g, which are not exactly equal. If needed, after completion of the study the results of the UCD-method can be modeled as if they were also reported in mg/g to evaluate any consequences and to allow a fair comparison with the App-method.

Several strengths regarding the study design can be mentioned. This is the first large-scale implementation study to prospectively investigate the participation rate, yield and cost-effectiveness of population-based screening for albuminuria for the early detection of CKD and CVD risk factors. The study uses a randomized approach, randomizing participants into one of the two screening strategies. Therefore, we can evaluate and compare both methods with respect to user-friendliness, willingness to participate, yield, and cost-effectiveness. This will allow an evidence-based choice for the most promising method for further exploration. The study design is further strengthened by the fact that albuminuria is not assessed only once in the home setting, but that confirmation tests are incorporated to reliably test whether albuminuria is elevated before participants are invited for a costly and more burdensome visit to a screening center for elaborate screening of CKD and CVD risk factors. This is in accordance with prevailing guidelines and takes variation in albuminuria into account, limiting the chance of false-positive findings [23].

To summarize, the THOMAS study is a unique investigator-initiated, population-based randomized trial that prospectively investigates the participation rate, yield and cost-effectiveness of screening for albuminuria for the early detection of CKD and CVD risk factors in the general population. By evaluating and comparing two home-based tests to assess albuminuria, insight will be provided to decide which strategy is the most promising to be explored further. Thus, the results of the THOMAS study will contribute to an improved, structured approach to the early detection of CKD and CVD risk factors.

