## Introduction

Chronic kidney disease (CKD) is a public health problem with a rising global prevalence that currently exceeds 10% [1,2]. CKD may progress to kidney failure, requiring dialysis or transplantation [3]. Importantly, patients with CKD, even in the earliest stages, are at increased risk for cardiovascular disease (CVD) [4]. These sequelae result in an impaired quality of life, decreased life expectancy, and a high economic burden for society [3]. CKD often remains undiagnosed for a long time and therefore not treated [5]. Therefore, earlier identification of CKD is desired to allow a timely start of treatment to prevent progression and associated complications [6].

Traditionally, most attention to screen for CKD was focused on measuring kidney function. However, screening for impaired kidney function allows only late intervention. During the last two decades, it has become clear that increased albuminuria is a strong risk factor for progressive CKD. In addition, it also predicts CVD as a marker of generalized vascular endothelial damage [7–9]. In the PREVEND study, that was performed in 1997, 5.6% of the general population had confirmed elevated albuminuria (i.e., urinary albumin excretion (UAE) ≥ 30 mg/24h) [10]. In the majority of these subjects, elevated albuminuria was not known to these subjects nor their general practitioners (GP), and 79% of them also had hypertension, type 2 diabetes, or hypercholesterolemia. In 89% of these individuals, one of these comorbidities was not yet diagnosed. Additionally, it was found that screening for increased albuminuria identified patients with a preserved kidney function, but a more pronounced decline in estimated GFR (eGFR) thereafter [8], and a cardiovascular (CV) event rate twice as high as in normoalbuminuric patients with a similar CV risk factor profile [11].

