**Fig 4 pone.0279321.g004:**
[figure not shown]
App test kit and its components to be used in the App-method. Abbreviations: App, smartphone application.

If the first test result is negative (ACR < 3 mg/mmol for the UCD-method; ACR <30 mg/g for the App-method), no further examinations are needed. However, if the first test result indicates increased albuminuria, participants are sent a second test kit for confirmation. When the result of the second test is negative, a third test is sent. In case the initial increased albuminuria result is confirmed by either the second or third test, the participant is invited for a visit to a screening facility where an elaborate screening follows. Reminders are sent to non-participating subjects three and six weeks after the initial invitations.

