#### Elaborate screening

Participants are asked not to perform any strenuous physical activity on the day before the screening and to complete a questionnaire. During the elaborate screening visit, height, weight, and blood pressure are measured, blood is drawn, and a spot urine sample collected. Blood pressure (mm Hg) and heart rate are measured four times using an automatic device (OMRON M7; OMRON Healthcare, Hoofddorp, The Netherlands) in a seated position on the non-dominant arm, of which the average of the last three measurements is reported. HbA1c, glucose, lipid profile, and creatinine are assessed in the blood samples. In the urine sample, albumin and creatinine are measured, and the ACR is calculated. Leftover urine and blood are stored in a biobank. The time of urine and blood sampling as well as fasting state of the participant are reported. During the elaborate screening, an internist-nephrologist is available for urgent medical questions. An overview of the measurements performed at the elaborate screening is provided in Fig 1.

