Risk factors are defined as abnormal in accordance with prevailing guidelines for Dutch GPs. Overweight is defined as a body mass index (BMI) >25 in case of age ≤70 years, and a BMI >28 in case of age >70 years. Hypertension is defined as a systolic blood pressure ≥140 mm Hg, diastolic blood pressure ≥90 mm Hg, and in case of a positive ACR, a systolic blood pressure ≥130 mm Hg and diastolic blood pressure ≥80 mm Hg [19]. Type 2 diabetes is defined as fasting plasma glucose ≥7.0 mmol/L, non-fasting plasma glucose ≥11.1 mmol/L, or a HbA1c ≥48 mmol/mol, (also in accordance with the American Diabetes Association (ADA) Guideline for diabetes [20]). For patients with known type 2 diabetes, inadequate regulation is defined as an HbA1c >53 mmol/mol in case of age <70 years, >58 mmol/mol in case of age >70 years and duration diabetes <10 years, and >64 mmol/mol in case of age >70 years and duration diabetes >10 years [19]. Prediabetes is defined as fasting plasma glucose of 5.6–6.9 mmol/L or HbA1c of 39–48 mmol/L in accordance with the ADA Guideline for diabetes [20]. An unfavorable lipid profile is defined as low-density lipoprotein (LDL) cholesterol >3.0 mmol/L in case of no other positive risk factors, >2.6 mmol/L in case of positive ACR or diabetes, or >1.8 mmol/L in case of cardiovascular disease history and age ≤70 years [21]. Impaired kidney function is defined as an eGFR (using the creatinine-based Chronic Kidney Disease Epidemiology (CKD-EPI) Collaboration equation) <60 ml/min/1.73 m^2^ [22,23].

Participants and their GP receive the results of the elaborate screening by mail. When abnormalities are found that warrant treatment according to the prevailing GP guidelines, participants are referred to their GP to be prescribed lifestyle measures (e.g., to lose weight and/or stop smoking) and/or medical intervention. This is also the case when participants are already known with having these risk factors, but appear to be poorly controlled. If no abnormalities are found other than albuminuria, participants receive a letter with the screening results and a recommendation to visit their GP one year later for repeat screening of albuminuria and CVD risk factors, again in accordance with prevailing guidelines.

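### The article promises CKD prevalence for the Netherlands, but kidney function is measured only in people with confirmed albuminuria, so the design can support a prevalence of confirmed albuminuria only

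*Protocol article*

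**What the plan says.** In the Discussion, the last of the reasons for inviting everyone, rather than only people without known risk factors, is that "the study will provide up-to-date information concerning albuminuria and CKD prevalence in the Netherlands". CKD prevalence is named there alongside albuminuria prevalence.

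The design sections set out who gets which measurement:

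- **Home-based screening.** A first negative result ends the pathway: "ACR <30 mg/g for the App-method), no further examinations are needed". The UCD arm has the same rule at its own cut-off. Beyond that, "In case the initial increased albuminuria result is confirmed by either the second or third test, the participant is invited for a visit".
- **Elaborate screening.** Blood is taken at this visit: "HbA1c, glucose, lipid profile, and creatinine are assessed in the blood samples". "Impaired kidney function is defined as an eGFR" below 60 ml/min/1.73 m², from the creatinine-based equation.
- **Sub-studies.** The false-negative sub-study repeats urine tests. The lower cut-off sub-study leads to the elaborate visit only after positive second and third tests.
- **Discussion, limitations.** The article concedes that some people with CVD risk factors will not be found. On CKD it says that "the diagnosis of CKD is based on an initial positive test that has to be confirmed, which by definition implies CKD".

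**The concern.** The article treats albuminuria and kidney function as two separate markers. It gives impaired kidney function its own definition, and the Introduction reports that albuminuria screening picked up people whose kidney function was preserved. The two markers therefore need not select the same people.

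A prevalence of CKD needs both markers in everyone, or in a sample that represents everyone. Here the second marker is obtained only in people already positive on the first. Someone with an eGFR below 60 and a normal ACR leaves the study after one urine test, with kidney function unknown.

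The limitations paragraph does not mention this. It warns about missed CVD risk factors but gives no matching warning about missed CKD, so a reader could take the CKD ascertainment to be complete. At stake is a national CKD prevalence that would be quoted from a large randomised study although the design cannot estimate it.

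**Working it through.** The article gives no prevalence estimate to reproduce. The check has three parts: how many people would have an eGFR, how large the unseen part could be, and what else could move the estimate.

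**Inputs (Sample size section).** 15,032 invited; 50% take part in home-based screening; 8% of participants have an elevated ACR; 90% of those are confirmed; 90% of the confirmed attend elaborate screening.

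**1. Who has an eGFR**

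- Participants: 15,032 × 0.50 = 7,516
- Elevated ACR: 7,516 × 0.08 ≈ 601
- Confirmed: 601.28 × 0.90 ≈ 541
- Attend the visit: 541.15 × 0.90 ≈ 487

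An eGFR would be known for 487 / 7,516 = 6.5% of participants and 487 / 15,032 = 3.2% of invitees. All of them have confirmed albuminuria. The sub-studies add no eGFR in people without it.

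**2. Size of the unseen part, among participants**

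The design records 0.08 × 0.90 = 7.2% with confirmed albuminuria. The other 92.8% have no eGFR. Let x be the share of that 92.8% with eGFR below 60. Then

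- true CKD prevalence among participants = 7.2% + 92.8% × x
- understatement = 0.928 × x

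The article gives no value for x, so the values below are assumptions.

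| Assumed x | True CKD among participants | Understatement (points) | Share captured |
|---|---|---|---|
| 1% | 8.1% | 0.9 | 89% |
| 3% | 10.0% | 2.8 | 72% |
| 5% | 11.8% | 4.6 | 61% |

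Over the wider range of x from 0.5% to 8%, the captured share runs from 94% down to 49%.

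**3. Other influences on a population figure**

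*Participation.* With half of invitees taking part, the recorded 7.2% would equal the true value for all invitees only if prevalence q in non-participants satisfied (true value in participants + q) / 2 = 7.2%. At x = 1%, 3% and 5% this needs q = 6.3%, 4.4% and 2.6%, which is 77%, 44% and 22% of the prevalence in participants. Selection could also act the other way and widen the gap.

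*App false positives.* The Home-based screening section gives sensitivity 98.4% and specificity 92.9% for the App test. If errors on repeat tests were independent (an assumption), the confirmed false-positive rate would be 0.071 × (1 − 0.929²) = 0.97%, and the confirmed true-positive rate 0.984 × (1 − 0.016²) = 98.4%. A true 7.2% would then be recorded as 0.072 × 0.984 + 0.928 × 0.0097 ≈ 8.0%. Albuminuria prevalence in that arm could thus be too high, not too low.

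**The case against.** The strongest reply is that this is one sentence in the Discussion. It comes after a logistical and a clinical reason for the same choice, and it promises only information on prevalence. Prevalence is not among the primary, secondary or cost-effectiveness outcomes and plays no part in the sample size. Not measuring eGFR in everyone is also a reasoned choice: the Introduction argues that screening on kidney function allows only late intervention. All of this stands, and it makes the point minor. It does not make the sentence correct.

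A second reply is that no passage labels test-negative people as free of CKD. That is right. The statement that "the diagnosis of CKD is based on an initial positive test that has to be confirmed, which by definition implies CKD" makes confirmed albuminuria sufficient for CKD, not necessary. But no other source of CKD cases among test-negative people is described, so a CKD prevalence could be built only from the albuminuric ones.

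A third reply is that adjustment for non-participation may sit in the full protocol or analysis plan, which are not shown, and that the article already plans to compare participants with non-participants. This is accepted: the absence of weighting is not a finding. No analysis plan could supply the missing eGFR measurements.

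Two stronger readings are tempting:

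- A reader might set 7.2%, or the earlier cohort's 5.6%, against the Introduction's CKD prevalence of over 10% and infer that 28% to 44% of CKD goes unseen (1 − 7.2/10 and 1 − 5.6/10). The documents do not support this. The 7.2% is a planning assumption for people aged 45–80, the 5.6% comes from a 1997 cohort using 24-hour excretion, and the 10% is a global figure.
- A reader might infer that the usual-care arm of the cost-effectiveness model would be wrong. The article says that study data and literature data enter the model, but nowhere that a CKD prevalence from this study does.

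**Conclusion.** The concern holds in a limited form. The Discussion attributes to the study a result that the design cannot give. It can estimate the prevalence of confirmed elevated albuminuria among participants, but not CKD prevalence.

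Among participants, and taking each confirmed positive as CKD as the article does, the missing eGFR can act in one direction only: an understatement of 0.928 × x, with x unknown. The 0.9, 2.8 and 4.6 points are illustrations that rest on assumed values of x and on the planning rates. For the invited population or the country, one might infer that any published figure must be too low. That goes too far, because selection may act either way and App false positives act upward, so the net direction is unknown.

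Severity is minor. Participation rate, yield and the comparison of the two screening methods do not depend on this claim.

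**What to change.** 1. In the Discussion, restrict the claim to the prevalence of confirmed elevated albuminuria (albuminuric CKD) among participants aged 45–80 in the study region, and withdraw the claim about CKD prevalence.
2. Add to the limitations that people with an eGFR below 60 and normal albuminuria are not detected.
3. Report eGFR below 60 only as a proportion of albuminuria-positive people who attended elaborate screening.
4. If an albuminuria prevalence for the population is reported, give it separately by test method, both crude and standardised to the full invited sample by age, sex and postal-code class. Date of birth, sex and address are already held for every invitee (Study setting and population).

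The cost is a few sentences and, if item 4 applies, one standardised estimate per method from existing data. The downsides are that one advertised by-product of the study is given up and that standardising widens the interval slightly. No new measurement is needed, and data collection was still under way when the article was written, so the reporting can still be changed.
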